##### Criteria for Discontinuation or Withdrawal of Participants During the Study

The IST progression protocol (Table 2) shall be applied in a standardised manner, with no individualised modifications to the progression. Persistent inability to follow the prescribed protocol, including unresolved mild discomfort, shall be managed by considering the following criteria for discontinuation or withdrawal:Voluntary withdrawal by the participant: Participants may withdraw at any time and for any reason, as informed in the consent, without penalty or impact on the participant’s medical care.Development or worsening of medical conditions: If, based on the medical judgement of the team or staff, a new condition or the worsening of a pre-existing condition contraindicates continuation with the IST or significantly increases the risk, participants may withdraw from the programme.Adverse events (AEs): Occurrence of a Serious Adverse Event (SAE) or persistent/considerable AE related to participation, which, based on the medical judgement of the principal investigator or study doctor, makes it inadvisable to continue. All these occurrences will be recorded and evaluated according to the safety protocol.Non-compliance with protocol:○Failure to complete a minimum of 90% of the sessions, even after considering the extension of the period.○Persistent inability or refusal to perform exercises according to instructions and proper technique, compromising safety or validity, despite supervision and correction.○Failure to complete scheduled assessments within 20 weeks.Significant lifestyle changes or concomitant treatments: Initiation of unrelated intense exercise, drastic unsupervised dietary changes, or medical treatments that significantly interact with outcomes or safety, as assessed by the research team.Failure to engage in follow-up sessions: If the participant becomes unresponsive and does not attend sessions/assessments, despite reasonable attempts at contact, discontinuation will be considered.

The main reason will be documented in all cases of discontinuation or withdrawal. Data collected up to that point will be securely retained and considered for inclusion in statistical analyses (e.g., intention-to-treat), as described in the ‘Statistical Analysis’ section. Participants who discontinue the intervention will be able to continue with scheduled assessments if they wish to do so, provided that this is feasible.

#### 2.1.3. Control Mechanisms for Field Protocol Standardisation

To ensure a standardised and rigorous implementation of the protocol and the quality of the data, the following control mechanisms will be put in place:Training of Research Staff: All staff directly involved in the intervention and evaluation (principal investigator, evaluation professionals, qualified personal trainer) will receive specific and detailed training on all study procedures. The ‘qualified personal trainer’ should have a degree in Physical Activity and Sports Science or Physiotherapy, with demonstrable experience in working with older adults and strength training. Training will cover: consistent application of inclusion/exclusion criteria; accurate technique for individualised determination of joint angles (HALO© digital goniometer); correct instruction, supervision and progression of IST exercises (CIEX System machine, Chronojump software with feedback); standardised administration of questionnaires; and accurate performance of all assessment tests. Recalibration sessions or periodic team meetings may be held to ensure consistency.Standardisation of the Intervention (IST Programme): The application of the IST will strictly follow the set progressive 16-week design (single set per muscle group, gradual increase of total stimulus duration and intensity of submaximal phases), as detailed in Table 2. The correct technical performance of the 8 specific exercises will be guided by the standards provided in Figure 1 and Table 3. The use of the CIEX SYSTEM machine with real-time feedback is essential in ensuring that target intensities are met. All sessions will be held individually and will be directly supervised by qualified personnel.Standardisation of Assessment Procedures and Minimisation of Bias: To minimise potential bias during assessments, standardised protocols for each test and data collection (detailed in Section 2.2) will be strictly followed, including specific recommendations (e.g., EWGSOP, InBody manufacturer). All assessment personnel shall be trained. Calibrated instruments and objective measures (CIEX System, InBody 230, Newtest Powertimer) shall be used. As far as possible, assessors will not have access to the previous results of participants to avoid expectation bias. If the analysis of the static posture photographs is conducted by a different individual, an effort will be made to blind them to the time point (pre/post) during the assessment. Although complete blinding of primary assessors at the time point is difficult in this design, strict adherence to protocols and the use of objective measures are the primary strategies to reduce observer bias.Monitoring of Adherence, Compliance and Concomitant Variables: Attendance to training sessions and assessments will be recorded in detail, and adherence to protocol criteria will be continuously monitored (e.g., ≥90% sessions, assessments on time). Changes in usual medication (by asking at assessments and training visits) will be recorded by referring to the baseline information in Section 2.1.1. Participants will be instructed to maintain their usual dietary and physical activity habits, not initiating new diets or intense exercise programmes; compliance will be monitored informally, and significant changes will be recorded. Standardised Case Report Forms (CRFs) will be used and made available for ethical consultation or audit if required.Strategies to Promote Retention and Completion of Follow-up: Individualised and flexible scheduling, close supervision with motivational support, regular communication, and the possibility of extending the intervention period to make up for excused absences will be used to promote retention. The importance of completing all phases will be explained. If a participant discontinues the IST, they will be encouraged to complete the post-intervention assessment (week 17) if feasible, to collect outcome data from as many participants as possible (providing intention-to-treat analysis). Data collected until withdrawal will be retained and managed according to the Section 2.3 (‘Statistical Analysis’).

These mechanisms aim to minimise variability in implementation and ensure data reliability.

#### 2.1.4. Data Management

The following plans will be implemented for the data management of the study:Standardised Case Report Forms (CRFs): Standardised (physical or digital) CRFs, designed specifically for this study, will be used for all variables. These CRFs will be available for ethical or audit consultation if necessary.Data Entry: Data from physical CRFs will be entered into a Microsoft Excel database. To ensure data quality, a second team member will thoroughly double-check all entered data against the original forms.Data Coding: Variables will be coded according to a pre-established data dictionary to ensure consistency. Personally identifiable data will be excluded from the analysis database, using anonymised participant identification codes instead.Data Quality: In addition to input verification, range and logical consistency checks will be performed to identify errors or outliers. Any inconsistencies will be reviewed and corrected in consultation with the original CRFs or measurement staff. Periodic data quality reviews shall be performed.Data Security and Storage: All data (physical forms and electronic database) will be stored securely. Electronic data will be stored in password-protected institutional computers, with access restricted to the principal investigator’s team. Regular encrypted backups will be performed and placed in a secure, locked external hard drive. Paper forms and informed consents will be stored under lock and key at Baigene S.L. In compliance with institutional regulations, good research practice, the EU General Data Protection Regulation (GDPR) and applicable Spanish legislation, all study data will be securely stored for a minimum of 15 years following the completion of the trial.

#### 2.1.5. Assignment of Intervention and Blinding

Assignment of Intervention: This study employs a single-arm design where all participants receive the IST intervention. Therefore, no randomisation procedures, allocation concealment or implementation mechanisms will be applied to assign participants to different groups, as there is only one intervention group to which all eligible consenting participants will be assigned.Blinding:○Participants and Intervention Staff: Given the design and nature of the intervention (physical exercise), neither the participants nor the staff administering the IST (qualified trainer, principal investigator) will be blinded.○Outcome Evaluators and Data Analysts: Measures will be implemented to minimise evaluator bias (detailed in Section 2.1.3). Although complete blinding of lead assessors at the time point (pre/post) is difficult, attempts will be made to ensure that they do not access previous results when making subsequent measurements. For the analysis of static posture photographs, blinding of the analyst at the time of assessment will be attempted. Where possible, the primary statistical analysis shall be performed by a team member not involved in direct data collection; otherwise, the team will seek to analyse the primary data without knowledge of the temporal coding until preliminary analyses are completed, if feasible.Unblinding Procedure: Since there is no blinding of participants or staff to different treatment arms and the intervention is known, formal unblinding procedures are not applicable. In case of a serious adverse event, its relationship to the known IST intervention will be assessed according to safety protocols.

### 2.2. Assessment

The evaluation in this study will investigate the impact of the IST programme on the primary and secondary outcome variables detailed in Section 2.2.1. These variables encompass key indicators of sarcopenia, dynapenia, functional capacity, quality of life, and applicability and safety of the protocol in older adults. The outline of the pre- (week 0) and post-intervention (week 17, after 16 weeks of IST) assessments is described below. It is designed to obtain a comprehensive profile of each participant and measure the changes induced by the programme. Both phases will be conducted by a physical activity professional and the research group’s doctor.

#### 2.2.1. Study Outcome Variables (Outcomes)

The following variables will be assessed at pre- and post-intervention (week 0 and week 17, unless otherwise stated) to determine the efficacy and applicability of the IST, as distinguished from the eligibility measures (Section 2.1.1):A.Primary Outcome Variables (Assessment of reversal of dynapenia and sarcopenia):
1.Change in MVIC Knee Extensors:○Specific measurement variable: MVIC of the knee extensors, measured in Newtons (N) with the CIEX SYSTEM machine.○Analysis metric: Absolute change (MVIC_week17_–MVIC_week0_)○Method of aggregation: Mean and Standard Deviation (SD) of the change. The percentage change will also be calculated.○Time point(s): Baseline (week 0) and post-intervention (week 17) assessments.○Clinical Relevance: Knee extensor strength is key to functionality and independence in older adults; its improvement indicates reversal of dynapenia.2.Change at ASMMI:○Specific measurement variable: ASMMI (ASMM in kg/height^2^ in m^2^), measured by bioimpedance (InBody 230).○Analysis metric: Absolute change (ASMMI_week17_–ASMMI_week0_)○Method of aggregation: Mean and SD of change.○Time point(s): Baseline (week 0) and post-intervention (week 17) assessments.○Clinical Relevance: Fundamental diagnostic criterion for sarcopenia (EWGSOP2); an increase indicates improvement in the amount of muscle, essential for metabolic health and reduced frailty.
B.Secondary Outcome Variables
1.Other Indicators of Sarcopenia and Dynapenia:○Handgrip Strength: Specific measurement variable: Maximal handgrip strength, measured in kilograms (kg) (Jamar Dynamometer). Analysis metric: Absolute change from baseline to week 17. Method of aggregation: Mean and SD. Time point(s): Baseline (week 0) and post-intervention (week 17). Clinical Relevance: A component of the sarcopenia diagnosis and a predictor of functionality and mortality.○Gait Speed: Specific measurement variable: Usual gait speed over a 4 m course, measured in meters/second (m/s) (Newtest Powertimer). Analysis metric: Absolute change from baseline to week 17. Method of aggregation: Mean and SD. Time point(s): Baseline (week 0) and post-intervention (week 17). Clinical Relevance: A measure of physical performance, a component of the sarcopenia diagnosis, and a predictor of adverse outcomes.○MVIC of other muscle groups: Specific measurement variable: MVIC for the peck deck, pull over, lateral shoulder elevation, leg curl, low back, hip abduction and hip adduction, measured in Newtons (N) (CIEX SYSTEM). Analysis metric: Absolute change from baseline to week 17. Method of aggregation: Mean and SD of the change per exercise. Time point(s): Baseline (week 0) and post-intervention (week 17). Clinical Relevance: Assesses the training response across different body regions.○Sarcopenia Status: Specific measurement variable: Diagnostic status of sarcopenia according to EWGSOP2 criteria (based on muscle strength, muscle mass, and physical performance). Analysis metric: Change in the proportion of participants meeting the diagnostic criteria from baseline to week 17. Method of aggregation: Frequencies and percentages. Time point(s): Baseline (week 0) and post-intervention (week 17). Clinical Relevance: Quantifies the overall impact of the intervention on the diagnostic status of the condition.2.Health-Related Quality of Life (HRQoL):○Specific measurement variable: The index score derived from the EQ-5D-5L descriptive system and the Visual Analogue Scale (VAS) score of the same questionnaire. Analysis metric: absolute change from baseline to week 17 for both the index score and the VAS score. Method of aggregation: Mean and SD of the changes. Time point(s): Baseline (week 0) and post-intervention (week 17). Clinical Relevance: Measures the overall self-perceived health and the impact of the intervention on multiple dimensions of participant well-being.3.Applicability of the IST Protocol:○Perceived Safety: Specific measurement variable: Score on a 5-point Likert scale for perceived safety. Analysis metric: Mean score post-intervention. Method of aggregation: Mean and SD. Time point(s): Post-intervention (week 17). Relevance: Assesses the participant’s subjective perception of safety, providing data to test hypothesis H1.○Acceptance/Satisfaction: Specific measurement variable: (1) Adherence rate (% of completed sessions); (2) Score on a 5-point Likert scale for overall satisfaction. Analysis metric: Percentage for adherence; Mean score post-intervention for satisfaction. Method of aggregation: Percentage for adherence; Mean and SD for satisfaction score. Time point(s): Adherence monitored continuously during the intervention (weeks 1–16); Satisfaction assessed post-intervention (week 17). Relevance: Measures the feasibility and appeal of the intervention to participants, providing data to test hypothesis H2.○Perceived Difficulty: Specific measurement variable: Score on a 5-point Likert scale for perceived difficulty. Analysis metric: Mean score post-intervention. Method of aggregation: Mean and SD. Time point(s): Post-intervention (week 17). Relevance: Evaluates the perception of technical simplicity, providing data to test hypothesis H3.○Adverse events: Specific measurement variable: Incidence, type, severity and causality (relationship to IST). Analysis metric: Frequencies and descriptive summary. Method of aggregation: Counts and percentages. Time point(s): Monitored continuously during the intervention period (weeks 1–16). Relevance: Assesses the objective safety profile of the protocol, providing data to test hypothesis H1.

* Relevance (common to the previous 4): To evaluate the feasibility, safety, acceptability and perceived difficulty of the IST protocol from the participants’ perspective.

4.Static Posture Parameters:○Specific measurement variable: Key angular and alignment parameters of static posture (e.g., craniovertebral angle, shoulder symmetry, pelvic tilt), assessed from photographs using Kinovea^®^ software. Analysis metric: Absolute change from baseline to week 17, measured in degrees or centimetres. Method of aggregation: Mean and SD of the change for each parameter. Time point(s): Baseline (week 0) and post-intervention (week 17). Clinical relevance: Improvements in postural alignment may be associated with reduced musculoskeletal pain and better overall physical function.5.Physiological Variables at Rest:○Specific measurement variable: Resting systolic blood pressure (SBP) and diastolic blood pressure (DBP) in mmHg, heart rate (HR) in bpm, and peripheral oxygen saturation (SpO2) in %. Analysis metric: Absolute change from baseline to week 17. Method of aggregation: Mean and SD of the changes for each variable. Time point(s): Baseline (week 0) and post-intervention (week 17). Clinical relevance: These variables are monitored primarily for participant safety. Additionally, based on evidence that isometric training may positively influence resting blood pressure (BP) over the medium term [79,80], changes in SBP and DBP will be analysed as a secondary outcome of clinical interest.

C.Exploratory Outcome Variables

Genetic Association: Analysis of the association between selected genetic polymorphisms and the magnitude of the IST response in primary and secondary outcomes. This will be explored using regression models or genotype group comparisons.Other Descriptive Variables: Baseline data from the CGA and laboratory analyses will be used to characterise the sample and to explore other potential factors associated with the training response.

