## 2. Methodology

### 2.1. Design of the Intervention Study

This non-randomised, single-group, pre-post-intervention, exploratory trial will evaluate the impact of IST on sarcopenia and dynapenia in adults over 70 years of age across a 16-week period. A detailed timeline of enrolment, interventions, and assessments is presented in Table 1. Each participant will act as their own control, comparing their baseline and post-intervention status. A concurrent comparison group will not be included in this phase, which will focus on feasibility and preliminary effects (see Section 4 for a discussion of limitations). Allocation to different intervention groups is not applicable. The study aims to measure the effectiveness of IST in improving muscle mass, strength and quality of life, as well as its practical applicability. Participants will be recruited in Vitoria (Alava) and Zamudio (Bizkaia, Spain) through Baigene S.L., the Judizmendi Civic Centre (Vitoria-Gasteiz City Council) and the Estadio Vital Fundazioa Foundation.

**Table 1 healthcare-13-01573-t001:** Timeline for Study Participation.

Study Phase	Main Activities	Approximate Timing
Recruitment	Identification of potential participants, initial contact through the collaborating organisations (BAIGENE S.L., Judizmendi Civic Centre, Fundación Estadio Vital Fundazioa).	Prior to the start of the study
	1st Meeting (Information and Consent): Detailed explanation of the study, objectives, exercises; signing of the informed consent form.	Approx. 2–3 weeks before baseline assessment
	2nd Meeting (Criteria Evaluation): Questionnaire (sociodemographic, habits, pathologies, medication); Comprehensive Geriatric Assessment (CGA); Review of analytical data; Anthropometric measurements and Body Composition (height, weight, BMI, InBody for SMM/ASMM); Diagnostic tests for sarcopenia (gait speed, grip strength, and confirmation of low muscle mass with ASMM/ASMI) according to EWGSOP criteria.	Approx. 1–2 weeks before baseline assessment
Baseline Assessment	(Pre-Intervention Assessment): Measurement of physiological variables (BP, HR, SpO2), functional capacity (MVIC of 8 muscle groups, static posture), quality of life (EQ-5D-5L), saliva sampling for genetic analysis.	Week 0 (one week before the start of the IST)
Intervention	IST Programme: 2 sessions/week, 30 min/session, supervised. Progression according to Table 2	Weeks 1 to 16

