##### Diagnostic Tests for Sarcopenia (According to EWGSOP Criteria)

Specific diagnostic tests based on the EWGSOP criteria [2,3] will be performed to confirm the diagnosis of sarcopenia, a fundamental inclusion requirement:Running speed: This will be measured with a Newtest Powertimer system (Model 3000). Two series of 4 m will be performed, with the best result being chosen. Inclusion criteria: <0.8 m/s.Manual grip strength: This will be obtained with a Jamar dynamometer (Model 5030 J1) following a standardised protocol [3,77]. The dominant hand (or the contralateral hand if this is not possible) shall be used, with the participant seated and their elbow at 90°. The highest value of the three measurements (1-min interval) will be recorded. Inclusion criteria: males < 30 kg; females < 20 kg.Skeletal Muscle Mass: The acquisition of Skeletal Muscle Mass (ASMM or ASMMI using InBody 230) was described in the previous section (‘Anthropometric Measurements and Body Composition’). Inclusion criteria: men < 8.31 kg/m^2^ (ASMMI); women < 6.68 kg/m^2^ (ASMMI).

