#### 2.2.3. Post-Intervention Evaluation

A final assessment will be performed one week after completion of the 16-week IST programme (week 17). All baseline measurements (physiological variables, functional capacity including MVIC and posture, quality of life by EQ-5D-5L, and the components of the sarcopenia diagnosis) will be repeated to assess any changes induced by the training, with the exception of the genetic analysis, which is only performed at baseline. Additionally, applicability questionnaires (safety, acceptance and perceived difficulty using Likert scales) [87] will be administered to assess the IST protocol.

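### ASMMI (primary), handgrip, gait speed and sarcopenia status are defined from a week-0 baseline that the visit schedule does not provide; using the screening value instead would bias change towards improvement

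*Protocol article*

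**What the plan says.** **Outcome definitions (Section 2.2.1).** Outcomes are assessed at week 0 and week 17, "as distinguished from the eligibility measures (Section 2.1.1". The second primary outcome is "Absolute change (ASMMI_week17_–ASMMI_week0", by bioimpedance. Grip is "Maximal handgrip strength, measured in kilograms (kg) (Jamar Dynamometer). Analysis metric: Absolute change from baseline to week 17" and gait speed is "Usual gait speed over a 4 m course, measured in meters/second (m/s) (Newtest Powertimer). Analysis metric: Absolute change from baseline to week 17". Sarcopenia status has the same two time points.

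**Schedule (Section 2.1, Table 1).** The week-0 row reads "Measurement of physiological variables (BP, HR, SpO2), functional capacity (MVIC of 8 muscle groups, static posture), quality of life (EQ-5D-5L", followed by saliva sampling. It contains no body composition, grip or gait test. These stand in the row for the second meeting, about one to two weeks before the baseline assessment, with "Anthropometric measurements and Body Composition (height, weight, BMI, InBody for SMM/ASMM" and the sarcopenia tests. Section 2.2.2, which describes the week-0 procedures, also omits all three.

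**Entry thresholds (Section 2.1.1).** For muscle mass: "Inclusion criteria: men < 8.31 kg/m^2^ (ASMMI); women < 6.68 kg/m^2^ (ASMMI". Grip must be below 30 kg (men) or 20 kg (women), and gait speed below 0.8 m/s.

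**Week 17.** Table 1 lists repetition of the sarcopenia tests as an item apart from repetition of the baseline measurements. Section 2.2.3 instead counts them among the baseline measurements: physiological variables, functional capacity, quality of life "and the components of the sarcopenia diagnosis) will be repeated to assess any changes".

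**The concern.** The outcome section promises a baseline for ASMMI, grip and gait speed that is separate from screening, and no scheduled visit delivers it. A team working from Table 1 or Section 2.2.2 would start training with only one pre-training value of each. That value would be the one on which the person was admitted for being low.

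A low value partly reflects error in the low direction. On re-measurement the group mean rises even if nothing has changed. In a controlled trial this shift would be expected in both arms and would cancel in the comparison. Here each participant is their own control and the test is a paired t-test or Wilcoxon test, so the shift would be counted within the training effect. Sarcopenia status is exposed in the same way. If status at entry serves as baseline, everyone starts positive, and the McNemar test can only register moves to negative.

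The limitations in Section 4 name natural progression, Hawthorne effects and uncontrolled variables, but not regression to the mean. Once training has started, a missing baseline cannot be recovered.

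**Working it through.** **1. Where each outcome is measured before training**

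| Outcome | Baseline in 2.2.1 | Second meeting (Table 1) | Week-0 row (Table 1) | Section 2.2.2 | Used for entry |
|---|---|---|---|---|---|
| Knee-extensor MVIC (primary) | week 0 | no | yes | yes | no |
| ASMMI (primary) | week 0 | yes | no | no | yes |
| Handgrip | week 0 | yes | no | no | yes |
| Gait speed | week 0 | yes | no | no | yes |
| Sarcopenia status | week 0 | yes | no | no | yes |

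The gap covers exactly the variables used for selection.

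**2. The plan's own figure.** Section 2.3.1 gives N = 15 for a paired t-test with d = 0.80, two-sided α = 0.05 and 80% power. The exact noncentral-t power at N = 15 is 0.821, so the figure reproduces. With 15% losses, 15 / 0.85 = 17.6, hence 18. This calculation rests on quadriceps MVIC, which is scheduled at week 0 and is not an entry criterion, so it is not affected.

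**3. Expected shift if the screening value is the baseline.** Assume one normally distributed variable, test-retest reliability ρ, entry below the p-th quantile of those screened, and no true change. Then

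shift = (1 − ρ) × SD × φ(z_p) / p.

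The document gives neither ρ nor p; both are assumptions. For p = 0.30, z = −0.524 and φ(z) = 0.348, so φ(z)/p = 1.16. At ρ = 0.90 the shift is 0.10 × 1.16 = 0.116 SD.

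**4. False significant gain.** This is the simulated share of trials in which the paired t-test (two-sided 0.05) is significant in the upward direction with no true effect, at p = 0.30. Where a range is given, it spans two simulations of the same model.

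| ρ | Shift (SD) | Paired d | n = 15 | n = 18 | Above a single cut-off at week 17 |
|---|---|---|---|---|---|
| 0.90 | 0.116 | 0.26 | 16% | 18–19% | 21% |
| 0.95 | 0.058 | 0.19 | 10% | 11–12% | 15% |
| 0.98 | 0.023 | 0.12 | 6% | 6–7% | 9% |

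The nominal rate in that direction is 2.5%. The last column shows how many people would cross back over one threshold without any effect, which is what feeds the McNemar test.

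**5. Range.** Over p from 0.1 to 0.7 and ρ from 0.80 to 0.99, the false-gain rate at n = 15 runs from 3% to 55%.

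**6. With a separate week-0 value.** If its error is independent of the screening error, the expected shift is zero. The simulated two-sided rejection rate is then 0.047–0.052 for every ρ and p tried.

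**The case against.** The strongest reply is that the week-0 measurement is already prescribed. Section 2.2.1 gives week 0 as the time point for all these outcomes and separates them from eligibility, and Section 2.2.3 counts the sarcopenia components among the baseline measurements. On that reading, Table 1 and Section 2.2.2 merely fail to list three tests. This stands in part. A reader might infer that the plan definitely takes the screening value as baseline and so counts regression to the mean as a training gain. The document does not support that: it is self-contradictory, and the bias follows only if the schedule prevails. The reply does not remove the problem, because no visit provides for the repeat, and the week-17 row of Table 1 itself treats the sarcopenia tests as separate from the baseline measurements. Condensing for an article is a weak explanation, since Section 2.2.2 gives camera settings for posture but omits a primary outcome.

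A second reply concerns size, and it stands. A reader might apply the higher rates to ASMMI. The document gives no reliability for bioimpedance; if it is very repeatable, the shift is small. No rule for combining the three criteria is fixed either, so single-variable selection is only illustrative.

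Third, the trial is exploratory and admits that the lack of a control group weakens attribution. True, but this source of bias is avoidable within the present design. The ANCOVA mentioned in Section 4 is meant for lifestyle and medication variables and would not remove it.

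**Conclusion.** The contradiction is on the page: a week-0 baseline distinct from eligibility is asserted for ASMMI, handgrip, gait speed and sarcopenia status, and neither Table 1 nor Section 2.2.2 schedules the measurements for it. The consequence is conditional. If the screening value serves as baseline, the expected bias is towards improvement. Its size depends on reliability and on how far the cut-offs cut into the screened population, neither of which the document states. Under the assumptions above (30th percentile, n = 18, one selection variable, no true change), the false-gain rate is about 6–7%, 11–12% or 18–19% at reliability 0.98, 0.95 or 0.90, against 2.5%. One of the two primary outcomes is exposed; knee-extensor MVIC is not.

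The interval from screening to week 0 might look like an untreated control period. It is not one: Table 1 puts it at one to two weeks, against a pre-post interval of 17 weeks.

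**What to change.** Reconcile the passages before recruitment starts:

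- Add InBody body composition, handgrip and 4 m gait speed to the week-0 row of Table 1 and to Section 2.2.2, to be done after eligibility has been confirmed.
- State that change in ASMMI, grip and gait speed, and baseline sarcopenia status, are taken from these week-0 values. Screening values serve eligibility only. Someone whose week-0 value lies above a threshold then stays in the analysis, and the McNemar table can show moves in both directions.
- Name residual regression to the mean in Section 4. The two pre-training visits are only one to two weeks apart, so error shared between them would leave part of the shift in place.
- Optionally, report the screening-to-week-0 change descriptively as a check on regression to the mean, not as a control for the 17-week change.

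The cost is small: by my estimate a few minutes per participant, at a visit that already takes place and with devices the trial already uses, plus the text edits. The sample size does not change.
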